## INTRODUCTION

[figure not shown]

The overwhelming and crucial importance of achieving Universal Health Coverage (UHC), and other Health Related Sustainable Development Goals (HR-SDGs) in health policy discussions within the global health community is driving a proliferation of new estimates to track progress from increasingly complex analytical models. However, considerable limitations and uncertainty about quality remain regarding the primary input data on which these modelled estimates are based. This uncertainty extends to data to measure and evaluate many of the HR-SDGs. The UN agencies, such as World Health Organization (WHO), United Nations Children's Fund (UNICEF), The United Nations Population Fund (UNFPA) and the World Bank, institutions like the Institute for Health Metrics and Evaluation and Measure, and various donor agencies are contributing to the increasing volume and frequency of new data generation and estimates. These global health estimates are much needed and valuable tools in monitoring trends, predicting future health challenges, and guiding interventions. However, while considerable advances have been made, the efforts to generate results that will help to monitor progress towards the HR-SDGs (which go beyond SDG 3) and UHC also obscure a rather critical weakness in the analytical foundations: namely, there is sparse empirical data that can be used as the basis for the sophisticated modelling required – or to inform national policymaking. Additionally, the WHS+ will collect data on the determinants of health outcomes, including social determinants and household economic status, in order to provide the appropriate explanations for the differences in the health outcomes. The WHS+ will also collect data on subjective well-being to inform the relationship between health and well-being. While many existing surveys, such as the World Bank's Living Standards and Measurement Surveys, might collect some of this information in a piecemeal manner, the WHS+ will collect this data in an omnibus surveys to examine the relationships within the household and individuals who form the sample to provide insights that are otherwise unavailable.

The proliferation of health-related estimates is also driven in part by the growing number of organizations with their own programmatic goals, indicators and targets, including WHO's 13th General Programme of

Work (GPW13) Impact Framework. This framework includes the triple billion targets, one billion more people benefitting from universal health coverage, one billion more people better protected from health emergencies, and one billion more people enjoying better health and well-being by 2023, and 46 indicators for progress towards achieving the HR-SDGs, with a key focus on achieving UHC. These GPW13 indicators are aligned with the SDGs and UHC indicators but, nonetheless, require WHO member states to develop data reporting mechanisms. WHO recognizes that monitoring the multitude of indicators across many international agreements and national priorities will require robust data generation systems. WHO's GPW13, therefore, places a strong focus on the importance of open data systems, with emphasis on country-led and -owned data collection.

One proven method to improve population health estimates is through strengthening routine and periodic data generation efforts and national analytical capacity. WHO's recent SCORE assessment (<https://www.who.int/data/stories/score-global-report-2020--a-visual-summary>) has clearly demonstrated that a large number of low- and middle-income countries still lack strong data and health information systems to monitor the impact of interventions in a timely and effective manner. Strengthening these systems takes time and sustained attention.

One element of health systems strengthening includes implementation of multi-topic health surveys that provide robust and high-quality data for monitoring health trends and determinants. Household health surveys are a reliable method of addressing many data gaps and form a critical component of national data and health information systems. For instance, 80 of the 232 SDG indicators come from household surveys, according to the Inter-Secretariat Working Group on Household Surveys. These include 29 of the 59 health-related SDG indicators. The option of using any additional surveys to assess progress towards SDGs should, ideally, be integrated into a nationally-led, regular and coordinated system and schedule of household health surveys.

While most countries have some form of household health surveys as part of their data and health information system, especially in low resource settings these are heavily donor dependent and not nationally owned and institutionalized.

**WHO's World Health Survey Plus (WHS+) is proposed as the next generation of an integrated multi-topic, multi-mode household health survey for all member states learning from the experience of conducting household health surveys over the last two decades.**

The **WHS+** protocol and implementation plan builds on experiences from the 2003 World Health Survey (WHS) and longitudinal WHO Study on global AGEing and adult health (SAGE), which have provided national and sub-national level data for a number of countries. The WHS and SAGE studies were reviewed by WHO's ethical review committee as well as national institutional review boards. The data from these surveys still remain invaluable today in providing internationally comparable information in large datasets not available in other omnibus household health surveys. The foundations of the **WHS+** will also aim to build on and work with other large survey programmes, including the World Bank's Living Standards Measurement Study (LSMS) or Household Income and Expenditure Survey (HIES), USAID's Demographic and Health Surveys (DHS), UNICEF's Multiple Indicator Cluster Survey (MICS), and WHO's World Mental Health Survey.

## **AIMS AND OBJECTIVES**

The aim of the **WHS+** is to generate valid, reliable, comparable and timely information on a range of health and well-being outcomes and determinants of public health importance in nationally representative target populations. The results from the **WHS+** will support WHO member states to track progress on country-specific objectives and towards UHC and HR-SDG targets, and WHO's Impact Framework approved by Member States.

### ***Primary Objectives***

- 1) Create a robust multi-functional data collection platform for generating data to monitor progress on national priorities, HR-SDGs and UHC
- 2) Support countries to generate, analyse and use high-quality data to fill data gaps
- 3) Develop standardized, computerized data collection strategies that enable speedier data collection and more reliable comparison across countries.

### ***Additional Objectives***

- 1) Develop capacities in using evidence for policy
- 2) Institutionalize a regular data generation platform in countries
- 3) Provide tools and methods for better sequencing and coordination between studies
- 4) Pursue improvements in integrating survey data into health information systems
- 5) Provide methods for the inclusion of neglected topics and population groups
- 6) Build on post-census surveys with up-to-date sampling frames
- 7) Introduce a suite of data collection and analysis tools to use alongside National Statistics Offices and the United Nations Statistics Division

## **METHODOLOGY**

### ***Sampling and sample size***

The standard sampling design for the **WHS+** will be a nationally representative stratified multi-stage cluster sampling of households when traditional area-based sampling frames derived from a recent population census or large-scale household sample survey are available.

The sample size will be approximately 6000 households including a margin to support an expected non-response of up to 20 percent. A larger sample size will be considered if sub-national estimates are required.

The typical design will stratify the areas in the frame by regions that are specified as core domains of interest. For each of these regions, further area stratification may or may not take place, depending on the quality of the available frame information.

Sampling of areas defined as primary sampling units (PSUs) will be carried out using probability proportional to size (PPS). Typical size measures are numbers of households or residents from the most recent population census or some other similar source.

The number of PSUs to be selected in each stratum are obtained by dividing corresponding stratum sample sizes by the expected number of households an interviewer can cover during the time allocated for completing data collection work within a sampled PSU.

Sub-sampling of households in each sampled PSU will be carried out after updating the list of households in the PSU.

The **WHS+** will explore an alternate sampling frame approach – gridded population datasets – to improve and extend representativeness of the results. Especially where up-to-date sampling frames are unavailable, this approach helps to establish robust, representative study samples.

The sampling frame is defined based on micro-level population estimates. Satellite imagery and its derived products can be used to construct a population layer, using an easy, workable method that divides the area of interest into grids. The sampling design reflects the characteristics of the random field by

combining contextual stratification and is proportional to population size sampling. The parameters of the grid samples include coverage, frame, design, strata, target and sample size.

The WHS+ team will work with in-country colleagues to determine the most appropriate way of identifying the target population and then advise on how best to identify, select and contact the sample. Through this innovative and tailored approach, the WHS+ teams will be able to collect detailed, granular information about different population groups.

The units of analysis will be the household and individual. The target population is adults, 18 years and older, residing within individual households, institutionalized population excluded. Inclusion criteria are age 18 years and older (unless countries want younger populations included and can obtain ethical approvals and appropriate procedures for the WHS+ implementation) and ability to provide informed consent.

Prospective household surveys will use interview modes that best suit the country situation. The WHS+ will provide options to collect data in a number of different ways, taking advantage of the latest technologies for face-to-face computer assisted personal interviews (CAPI), computer-assisted telephone interviews (CATI) and online surveys. Translation and back-translation protocols, as per WHO's instrument translation guidelines, will be used to ensure a variety of main languages are available for the interviews in each country.

The type of data to be collected includes interview and biomarker data. The data collection period is open-ended, starting in 2022 for baseline surveys. A 5-year survey cycle will be pursued for repeat cross-sectional design surveys.

---

 Thomson et al Int. J Health Geogr (2020)19:34 <https://doi.org/10.1186/s12942-020-00230-4>

The household member who is most knowledgeable about the household will be invited to complete the household questionnaire as the household informant. The interviewers will be trained to identify the household member through a set of probing questions that will be clarified during the training and in the interviewer manual for the WHS+. This person will then be interviewed following informed consent. Eligible household members will be listed in the household roster and will be randomly selected by the CAPI or by the CATI programme, including approaches such as a random-digit dial, to complete the individual interview. Typically one eligible respondent will be selected to complete the individual questionnaire per household. When the module on reproductive and child health is included in the individual questionnaire, a second respondent, a woman of reproductive age, will be randomly selected to complete this module only if the initial eligible respondent is not a woman of reproductive age. The individual respondent will be an adult 18+ years in age and who gives consent to be interviewed.

When a country wants to implement a longitudinal cohort study the **WHS+** design will take this into account and the sample will be designed accordingly. In countries where there has been previous implementation of a longitudinal study like SAGE attempts will be made to follow up the previous sample and account for attrition.

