**Table 1. Example of the suite of standardized survey modules covering a range of thematic areas that countries could select to create their WHS+ instrument**

| Household                                                                       | Individual                                                                                                            | Special                                                                                        |
|---------------------------------------------------------------------------------|-----------------------------------------------------------------------------------------------------------------------|------------------------------------------------------------------------------------------------|
| Introduction and consent                                                        | Introduction and consent                                                                                              |                                                                                                |
| Recontact information                                                           | Sociodemographic characteristics                                                                                      | Community surveys, Structural determinants of health                                           |
| Household roster including health insurance coverage and immunization schedules | Health state (health status and functioning) and disability                                                           | Disability survey                                                                              |
| Housing (including water and sanitation and use of clean fuels)                 | Anthropometric measurements, performance tests (vision, hearing, gait speed, grip strength, cognition), blood tests   | Mortality – WHO Verbal Autopsy Questionnaires, birth history/ orphanhood, sibling survivorship |
| Household and family support networks and transfers                             | Health risks (tobacco, diet, physical activity, alcohol, social determinants of health, food insecurity, salt intake) | Violence against women, violence against children                                              |

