### ***Brief summary of potential analyses***

A table of the most recent household and population estimates by stratifiers (locality(urban/rural), region/state/province, sex, age-groups) will be required prior to starting interviews. Household weights for analysis at household level and individual weights for analysis at person level will be calculated. These weights will be based on the selection probability at each stage of sampling.

Household weights will be post-stratified by region/state/province and locality. Individual weights will be post-stratified by region/state/province, sex and age-groups (18-29, 30-39, 40-49, 50-59, 60-69, 70+). Post stratification adjustments will be based on the most recent household and population estimates provided by the National Statistics Office.

Weighted social and demographic characteristics of respondents will be summarized using descriptive statistics.

Further topic-specific analyses will be led by topical experts and adjusted for the complex survey design. Each module will include guidance on how to compute key indicators linked to the UN SDGs or WHO Impact Framework, for example. Additional multi-variable modelling to examine individual-level and country-level variables, or sub-group analyses, associated with primary or secondary outcomes will be organized by the interested analyst. Analytical scripts will be generated and shared by WHO HQ to ensure results are reproducible – and to speed up the dissemination of results.

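### Inclusion requires ability to consent, yet the weights scale to all adults, so disability and functioning are understated for the stated target population by an unknown amount

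*Protocol*

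**What the plan says.** All references are to the protocol.

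- **Target population** (Sampling and sample size): "The target population is adults, 18 years and older, residing within individual households, institutionalized population excluded". Institutional residents are the only group carved out.
- **Inclusion criteria** (the next sentence): age 18 or over, with an allowance for countries that want younger people, ending "appropriate procedures for the WHS+ implementation) and ability to provide informed consent".
- **Respondent selection** (same section): "Eligible household members will be listed in the household roster and will be randomly selected by the CAPI or by the CATI programme". Then: "Typically one eligible respondent will be selected to complete the individual questionnaire per household". And: "The individual respondent will be an adult 18+ years in age and who gives consent to be interviewed".
- **Weights** (Brief summary of potential analyses): base weights come from the selection probabilities at each stage. Then "Individual weights will be post-stratified by region/state/province, sex and age-groups (18-29, 30-39, 40-49, 50-59, 60-69, 70", the last band being open-ended. The control totals are National Statistics Office estimates, with no stated restriction to adults able to consent.
- **Outcomes** (Data Collection): Table 1 offers an individual module, "Health state (health status and functioning) and disability". Cognition is among the performance tests.
- **Objectives** (Additional Objectives): "Provide methods for the inclusion of neglected topics and population groups".

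**The concern.** The target population and the inclusion criteria stand in adjacent sentences and do not describe the same people. A household resident with advanced dementia or severe intellectual disability belongs to the first and may fail the second. This is not ordinary undercoverage, because the reason for exclusion is closely tied to what the survey measures: functioning, disability and cognition.

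The weights then raise the interviewed adults to population totals that do not recognise the exclusion. A country report would present a disability prevalence for its adult household population when the estimate describes only adults able to consent. Because nothing says who judges capacity, or at what point, countries may also apply the criterion differently. That weakens the comparability the survey is meant to deliver.

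**Working it through.** The protocol gives no prevalence, design effect or share unable to consent, so there is no planned figure to reproduce. The check has two parts: whether the direction depends on when capacity is judged, and how large the bias could be.

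**1. Does the order matter?** Let *c* be the share of household adults unable to consent, *D* the true prevalence of a condition among all household adults, and *s* its prevalence among those unable to consent.

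- *Judged before the draw:* these adults have selection probability zero. The weighted estimate targets the mean among adults able to consent.
- *Judged after the draw:* a selected adult who cannot consent yields no interview. The weights as described carry no term for capacity or health, so the remaining interviews again target the mean among adults able to consent.

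Either way, setting other non-response aside:

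estimate = (D − c·s)/(1 − c), and bias = −c(s − D)/(1 − c).

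The bias is downward whenever s > D. The order affects whether the loss can be seen in the non-response records, not its direction.

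**2. Size.** From the protocol: about 6,000 households with up to 20% non-response, so 6,000 × 0.80 = 4,800 interviews at one adult per household. Assumed: design effect 2, s = 1 (everyone unable to consent has the condition), c = 0.25% or 1%, D = 2% to 15%.

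SE = √(D(1 − D) × 2/4,800). For D = 5%: √(0.05 × 0.95 × 2/4,800) = 0.445 points.

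With c = 1%: (0.05 − 0.01)/0.99 = 4.04%, a bias of −0.96 points, and 0.96/0.445 = 2.2 SE.

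| D | c | Estimate | Bias (points) | Bias/SE |
|---|---|---|---|---|
| 2% | 0.25% | 1.75% | −0.25 | 0.86 |
| 5% | 0.25% | 4.76% | −0.24 | 0.54 |
| 10% | 0.25% | 9.77% | −0.23 | 0.37 |
| 15% | 0.25% | 14.79% | −0.21 | 0.29 |
| 2% | 1% | 1.01% | −0.99 | 3.46 |
| 5% | 1% | 4.04% | −0.96 | 2.16 |
| 10% | 1% | 9.09% | −0.91 | 1.48 |
| 15% | 1% | 14.14% | −0.86 | 1.18 |

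If s is below 1, each bias shrinks in proportion to s − D.

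**3. Ages 70 and over.** Assuming D = 20% and s = 1, c = 2%, 5% or 8% gives 18.4%, 15.8% or 13.0%. At c = 5%: (0.20 − 0.05)/0.95 = 15.8%, a relative shortfall of 21%.

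**4. Does age post-stratification repair it?** An illustration over the six age bands, all inputs assumed and s = 1:

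- population shares 30, 22, 18, 14, 10 and 6%
- prevalence 2, 3, 5, 8, 14 and 30%
- excluded 0.3, 0.3, 0.4, 0.6, 1.2 and 5%

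True prevalence is 6.48%. The estimate is 5.79% without post-stratification and 5.86% with it. The repair is (5.86 − 5.79)/(6.48 − 5.79), about a tenth. The loss occurs within each cell, where weights by age, sex and region cannot reach it.

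**The case against.** The strongest reply is that this is a short umbrella protocol and that too much can be read into it. Several stronger readings are tempting and are not supported:

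- *Capacity is definitely screened before the draw.* A reader might infer this from the word eligible, but its meaning at the roster stage is not defined. The description of the respondent as someone who gives consent fits assessment after selection just as well.
- *Another household member replaces the excluded adult.* No substitution or redraw is described anywhere.
- *Incapacity goes unrecorded.* The Quality assurance section asks for detailed non-response information, which could capture it if capacity is judged after the draw.
- *Proxies are ruled out, or must be added.* The protocol is silent. It mentions an interviewer manual that is not shown and leaves ethics approval to each member state. Proxy interviewing is a trade-off, and it could not supply a cognition performance test.

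It is also fair to say that requiring consent is an ethical safeguard, not an error, that the affected modules are options countries may select, and that every figure above rests on assumed inputs.

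All of this limits the claim without removing it. The mismatch between target population and inclusion criteria is in the protocol itself, and the weights as described do not correct the loss under either order of assessment. A manual or analysis plan could add a proxy rule or an outcome code, but the two sentences would still disagree.

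**Conclusion.** The point holds as a mismatch between the stated target population, the eligibility rule and the weighting totals. Followed as written, disability and functioning, and cognition where measured, are understated for the stated target population. This rests on one substantive assumption: that adults unable to consent have these conditions more often than other adults. The effect is probably largest at the oldest ages.

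The size cannot be fixed from the document. Across the assumed prevalences, with everyone excluded having the condition and a design effect of 2, the national bias is about 0.2 points and below one standard error if 0.25% of adults are excluded. It is close to one point if 1% are, which is above two standard errors at 5% prevalence. Neither the illustration for ages 70 and over nor any single national figure should be read as an estimate for a participating country.

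**What to change.** **In Sampling and sample size:**

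- Make ability to consent a condition of self-interview, not of roster eligibility.
- List all resident adults aged 18 and over and draw from all of them.
- If the selected adult cannot consent, do not substitute. Record a separate outcome, *unable to consent*, distinct from refusal and non-contact.

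**In Brief summary of potential analyses:**

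- Report the weighted share unable to consent (*u*) by age and sex.
- Label disability, functioning and cognition estimates as covering adults able to consent.
- Add a sensitivity bound that counts those unable to consent as having the condition: u + (1 − u)·p, where p is the labelled estimate. With u = 1% and p = 4.04%, this gives 0.01 + 0.99 × 0.0404 = 5.0%, the true value in the worked case. If not all of them have the condition, it is an upper bound with respect to this exclusion.

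An ethics-approved proxy for observable functioning items may be offered as a country option, not a requirement.

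**Cost:** one disposition code, a small change to the selection program and slightly lower interview yield. At a 1% share that is about 0.01 × 4,800 = 48 interviews. A proxy option would add ethics work only in countries that choose it.
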